### Statistical calculations for trial sample size

The estimations in regard to the primary endpoint are derived from data from neoadjuvant cisplatin-based chemotherapy followed by radical cystectomy as current standard of treatment. In this regimen, the rate of patients with completed treatment (neoadjuvant therapy and radical cystectomy) is between 90 and 95% [21]. Trials of neoadjuvant radiotherapy in urinary bladder cancer showed no additional postoperative toxicity [2, 3]. Comparing the toxicity of Nivolumab to cisplatin, we assume that a completion rate of 90–95% is a reasonable estimation for the neoadjuvant radio-immunotherapy.

Assuming a rate ≥ 92.5% of patients with completed treatment at the end of week 15, we would tolerate an additional 22.5% of treatment delay (≥ 70% patients with completed treatment at the end of week 15). Thirty patients will be required to reject the null-hypothesis of a rate < 70% patients with completed treatment at the end of week 15 with 82% power and a 2-sided significance level of 5%. Additional 3 patients will be enrolled to account for possible drop-outs. This leads to a panned sample size of 33 patients. Recruitment will be conducted during a period of 2 years.

### Interim analysis

To ensure patient safety, a planned interim analysis will be performed after 11 patients, with review of an independent data safety monitoring board.

### Data analysis

All continuous endpoints will be summarized using descriptive statistics. All categorical endpoints will be summarized using absolute frequencies and percentages.

For the primary endpoint, an exact test for single proportions will be performed to reject the null hypothesis of ≥22.5% of treatment-related delay in surgery at week 15. Proportions will be displayed together with their 90% confidence intervals. If the resulting *p*-value is less than 5%, the study is considered successful. The primary analysis is based on the Full Analysis Set (FAS). Kaplan-Meier curves will be used to describe event-free rates over time (DFS, CSS and OS). Median event-free times will be reported with 95% CI, if the number of events allows the estimation of the median.

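### The primary test is written against a null of 22.5% delayed (77.5% on time), but the trial is sized against a null of 70% completed

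*Protocol article*

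**What the plan says.** Three places in the protocol article bear on the primary test.

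- **Primary endpoints.** The endpoint is the rate of patients who have completed both radio-immunotherapy and radical cystectomy by the end of week 15. Minimum numbers of nivolumab cycles and radiation fractions define completion.
- **Statistical calculations for trial sample size.** The expected rate is "92.5% of patients with completed treatment at the end of week 15". The text adds that "we would tolerate an additional 22.5% of treatment delay", and gives the result in brackets as at least 70% completed. It continues: "Thirty patients will be required to reject the null-hypothesis". The null so described is anything below "70% patients with completed treatment at the end of week 15 with 82% power", at a two-sided 5% level. Three further patients for drop-outs bring the total to 33.
- **Data analysis.** The primary analysis is an exact single-proportion test, whose stated purpose is "to reject the null hypothesis of ≥22.5% of treatment-related delay in surgery at week 15". The study is a success if the p-value is below 5%. Proportions are shown with 90% confidence intervals, and the analysis set is the Full Analysis Set.

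**The concern.** In the sample-size section, 22.5 is a margin. It is added to the 7.5% of patients already expected not to complete, so the null failure proportion is 7.5% + 22.5% = 30%. In the Data analysis section the same 22.5 appears as the whole null proportion. The reference to its being additional has gone, and so has the 70%. A test of one proportion takes one absolute null value, and as written that value is 22.5% failures, i.e. 77.5% on time.

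The variable differs too. A patient who receives too little radio-immunotherapy but has surgery on time fails the defined endpoint, yet is not a case of delayed surgery. A patient whose curative cystectomy is not done because imaging shows systemic disease (foreseen under Treatment and follow up) also fails the defined endpoint. Whether that is treatment-related delay is a matter of judgement.

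This test is the sole criterion of success. If both statements stand, some results give opposite verdicts, the 82% power does not belong to the test as written, and the choice between thresholds could be made after the data are seen.

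**Working it through.** **Inputs.** From the sample-size section: expected rate p1 = 0.925, null p0 = 0.925 − 0.225 = 0.70, two-sided 5%, n = 30 evaluable and 33 enrolled. From the Data analysis section: exact single-proportion test; literal null p0 = 1 − 0.225 = 0.775.

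**Method.** With X the number of completers, X ~ Binomial(n, p). The cut-off r is the smallest count with P(X ≥ r | p0) ≤ 0.025, the upper half of a two-sided 5% level. Power is P(X ≥ r | 0.925).

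**Step 1: reproduce the plan's figure.** For n = 30 and p0 = 0.70, P(X ≥ 26) = 0.0302 is too large and P(X ≥ 27) = 0.0093 qualifies, so r = 27. Power = P(X ≥ 27 | 0.925) = 0.8155, which rounds to the stated 82%. Other conventions miss it: one-sided 5%, or a two-sided exact test built by minimum likelihood, gives r = 26 and 93.0%; the two-sided normal approximation gives 89.8%; the arcsine method 91.2%. The trial was therefore sized with a 70% null and 2.5% in the upper tail.

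**Step 2: repeat with the null as written in the Data analysis section.**

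| Null completion rate | n | Cut-off | Upper-tail p at cut-off | Power at 92.5% |
|---|---|---|---|---|
| 70% | 30 | ≥27 | 0.0093 | 81.6% |
| 70% | 33 | ≥29 | 0.0149 | 90.2% |
| 77.5% | 30 | ≥28 | 0.0221 | 60.7% |
| 77.5% | 33 | ≥31 | 0.0122 | 54.5% |

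Like for like, power falls from 82% to 61% with 30 patients and from 90% to 55% with 33. Against 77.5%, the minimum-likelihood test gives the same cut-offs and powers. The first sample size to exceed 80% power against that null is 49 (≥44 of 49, power 84.1%).

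**Step 3: results that change verdict.** Each is compared with 0.025.

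| Result | Upper-tail p against 70% | Upper-tail p against 77.5% | Chance if the true rate is 92.5% |
|---|---|---|---|
| 27/30 | 0.0093 (success) | 0.0696 (failure) | 0.8155 − 0.6068 = 20.9% |
| 29/33 | 0.0149 (success) | 0.1066 (failure) | 0.9025 − 0.7675 = 13.5% |
| 30/33 | 0.0042 (success) | 0.0419 (failure) | 0.7675 − 0.5455 = 22.2% |

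With 33 patients, the chance of a result whose verdict depends on which section is followed is 0.9025 − 0.5455 = 35.7%.

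**The case against.** The best defence is that the Data analysis sentence is shorthand. The sample-size section has already defined 22.5% as extra delay and equated it with 70% completed. If treatment-related delay means delay beyond the expected 7.5%, the null is still 70% and the power still 82%. That is probably what was meant, so the loss of power belongs to the text as written and not necessarily to the intention. The sentence still does not say it, and it is the one from which the test would be programmed.

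Three further points qualify the figures.

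- **The level.** The Data analysis section gives only p below 5%, with 90% intervals, which would suit a one-sided 5% test. On that reading, with 33 patients, the cut-off against 77.5% is 30 (p = 0.0419; power 76.7%) and against 70% it is 28 (p = 0.0414). Then 30/33 no longer changes verdict, but 28/33 and 29/33 do. The conflict remains and its size changes. The sample-size section states two-sided 5%, and only 2.5% in the upper tail reproduces the 82%.
- **The variable.** The 61% and 55% combine the null of one section with the 92.5% completion rate of the other. If only treatment-related delay of surgery were counted, the expected failure rate need not be 7.5%. The protocol gives no figure for it, so power for that variable cannot be calculated.
- **The range.** Only one count (of 30) or two counts (of 33) change verdict. They are close to the expected result, however, which is why their combined probability is 21% or 36%.

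That the article condenses a fuller protocol is no answer: it prints both nulls, and they disagree.

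**Conclusion.** The concern holds. The Data analysis section states a different null hypothesis, on a different variable, from the one for which the trial was sized. Read literally, with completion as the variable, a true rate of 92.5% and the stated two-sided 5% exact test, power is 60.7% with 30 patients (against 81.6%) and 54.5% with 33 (against 90.2%). The results 27/30, 29/33 and 30/33 reverse the trial's conclusion. The intended null is almost certainly 70%, since only that value reproduces the 82%. The design itself is therefore sound and the error lies in the wording. Because that wording governs the only success criterion, it must be corrected before the primary analysis.

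**What to change.** Replace the null in the Data analysis section with one on the defined endpoint, for example: H0 is that the proportion of Full Analysis Set patients with completed treatment (as defined under Primary endpoints) by the end of week 15 is 70% or less; equivalently, 30% or more have not completed, for any reason. Delete the reference to 22.5% treatment-related delay in surgery.

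In the same sentence, repeat that the test is two-sided at 5% with 2.5% in the upper tail, and give the cut-offs: at least 27 of 30 or 29 of 33. The same rule gives 27 of 31 (upper-tail p = 0.0239) and 28 of 32 (p = 0.0189), should the analysis set fall between the two.

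The cost is one sentence in the protocol, carried into the analysis plan. No patients, visits or data are added, and the sample size stands.

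### The 90% interval for the primary completion rate does not match the two-sided 5% test that the trial is sized for, and for one borderline result at n = 30 or n = 33 it would contradict that test

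*Protocol article*

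**What the plan says.** Three statements in the protocol article bear on the primary decision.

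- **Statistical calculations for trial sample size:** the null is a completion rate below 70%, the assumed rate is at least "92.5% of patients with completed treatment at the end of week 15", and the design is "with 82% power and a 2-sided significance level of 5" per cent. "Thirty patients will be required to reject the null-hypothesis", and "Additional 3 patients will be enrolled to account for possible drop-outs", which gives 33.
- **Data analysis, test and success rule:** for the primary endpoint "an exact test for single proportions will be performed"; if the p-value "is less than 5%, the study is considered successful". Neither the sidedness nor the version of the exact test is given here. The primary analysis uses the Full Analysis Set.
- **Data analysis, interval:** "Proportions will be displayed together with their 90% confidence intervals". Median event-free times in the same section get 95% intervals. No reason is given for 90%.

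**The concern.** A 90% equal-tailed interval has its lower limit above 70% exactly when the upper-tail p-value is below 5%. A two-sided 5% equal-tailed test rejects upwards only when that p-value is below 2.5%. The displayed interval therefore belongs to a more lenient test than the sized one.

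In a single-arm trial readers will compare the lower limit with 70%. A borderline result could then look like success in the interval and fail the test. Because the success rule does not repeat the sidedness, the 90% level may also suggest to an analyst that a one-sided 5% test was meant. That would lower the number of completed treatments needed for success.

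**Working it through.** **Inputs.** From the sample size section: p0 = 0.70, p1 = 0.925, two-sided 5%, stated power 82%, 30 patients required and 33 enrolled. From Data analysis: exact test, p below 5%, 90% interval. Assumption: the Full Analysis Set holds between 30 and 33 patients.

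**Formulas**, for r completions among n, with X binomial:
- Upper-tail p = P(X ≥ r | n, 0.70). The doubled two-sided p is twice this.
- The minimum-likelihood two-sided p sums the probabilities, under 0.70, of all outcomes no more likely than r.
- Power of the rule X ≥ r is P(X ≥ r | n, 0.925).
- The Clopper-Pearson lower limit is the a-quantile of Beta(r, n − r + 1), with a = 0.05 for a 90% interval and 0.025 for a 95% interval. The upper limit is the (1 − a)-quantile of Beta(r + 1, n − r).

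**Step 1: reproduce the stated 82% at n = 30.**
- Equal-tailed two-sided 5%: P(X ≥ 26 | 0.70) = 0.0302 exceeds 0.025, and P(X ≥ 27 | 0.70) = 0.0093 does not. The cut-off is 27/30 and the power is 0.8155, which rounds to 82%.
- One-sided 5%: the cut-off is 26/30, with upper-tail error 0.0302 and power 0.930.
- Minimum-likelihood two-sided 5%: 26/30 has p = 0.047, so the cut-off is again 26/30 and the power 0.930.
- Normal approximation: power 0.898 two-sided, 0.965 one-sided.

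Only the equal-tailed two-sided exact rule gives the stated figure.

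**Step 2: compare interval and test around the cut-off.**

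| Result | 90% lower limit | Upper-tail p | Doubled p | Min.-likelihood p | 95% lower limit |
|---|---|---|---|---|---|
| 26/30 | 0.720 | 0.0302 | 0.060 | 0.047 | 0.693 |
| 27/30 | 0.761 | 0.0093 | 0.019 | 0.016 | 0.735 |
| 26/31 | 0.690 | 0.0627 | 0.125 | 0.116 | 0.663 |
| 27/31 | 0.729 | 0.0239 | 0.048 | 0.048 | 0.702 |
| 27/32 | 0.699 | 0.0510 | 0.102 | 0.084 | 0.672 |
| 28/32 | 0.736 | 0.0189 | 0.038 | 0.033 | 0.710 |
| 28/33 | 0.707 | 0.0414 | 0.083 | 0.085 | 0.681 |
| 29/33 | 0.744 | 0.0149 | 0.030 | 0.023 | 0.718 |

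- At 28/33 (84.8%) the 90% interval, 70.7–93.8%, excludes 70%, but the two-sided test does not reject under either version.
- At 26/30 (86.7%) the 90% interval, 72.0–95.3%, excludes 70%. The doubled p of 0.060 does not reject, and the minimum-likelihood p of 0.047 does. Only at n = 30 do the two versions give different cut-offs (27 against 26).
- At n = 31 and n = 32 the 90% interval and the two-sided test agree for every outcome.

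**Step 3: how likely the conflicting outcome is.**

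| True rate | P(26 of 30) | P(28 of 33) |
|---|---|---|
| 70% | 0.021 | 0.027 |
| 85% | 0.203 | 0.190 |
| 92.5% | 0.114 | 0.064 |

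**Step 4: the one-sided reading.** If p below 5% were one-sided, interval and test would agree. Success would then need only 26/30 (upper-tail error 3.0%, power 93.0%) or 28/33 (4.1%, 96.6%). The sized rule needs 27/30 (0.9%, 81.6%), and its equivalent at 33 patients is 29/33 (1.5%, 90.2%).

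**The case against.** The best defence is that the decision rule is fixed and does not use the interval. Success is a p-value below 5%, and the 90% interval is only displayed. The sidedness is stated once, in the sample size section, for the same endpoint and threshold, and the natural reading carries it over. The version of the exact test is a detail that an article may leave to the full protocol or the analysis plan.

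Most of this stands. It answers two stronger readings that a reader might reach:

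- **That the trial would have two opposing formal verdicts.** The article does not support this. Nothing in it makes exclusion of 70% by the interval a criterion.
- **That the software default decides success.** This is true only of 26/30. At 31, 32 and 33 patients both exact versions give the same cut-off, and 33 is the planned enrolment.

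What remains is not an omission. Both the 90% level and the two-sided 5% level are written down, and they do not correspond. Carrying the two-sided level over to the success rule, as the defence asks, is what leaves the 90% interval out of step. Reading the rule as one-sided rescues the interval but abandons the stated level and power. No reading makes the sizing, the success rule and the interval all fit.

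**Conclusion.** The point holds in limited form, at moderate severity. The sample size is correct: the 82% power is reproduced. The fault is the interval level, together with a success rule that does not repeat its sidedness.

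Under the two-sided reading the formal conclusion is unaffected, but the displayed interval would contradict it at 26/30 (doubled tail) or 28/33. At the assumed rate of 92.5% those outcomes have probability 11.4% and 6.4%; at a true rate of 85% they have about 20% and 19%. Under the one-sided reading the bar falls by one completed treatment at both n = 30 and n = 33.

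This rests on Clopper-Pearson intervals, on 30 to 33 analysed patients, and on 70% as the null value, as in the sample size section. Wilson intervals give the same picture: their 90% lower limits are 0.734 at 26/30 and 0.720 at 28/33.

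**What to change.** In Data analysis, give the primary proportion a 95% Clopper-Pearson interval. State that the study succeeds if the exact upper-tail p-value against 70% is below 0.025 (the equal-tailed two-sided 5% test), equivalently if the lower 95% limit exceeds 70%. List the resulting cut-offs: at least 27/30, 27/31, 28/32 or 29/33.

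Interval and test then agree by construction, the version of the exact test is settled, and the 82% power at n = 30 is kept. The cost is a change of wording and a somewhat wider displayed interval: at 28/33 the lower limit moves from 70.7% to 68.1%.

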### Ethics, informed consent and safety

This study is conducted in accordance with Good Clinical Practice (GCP), as defined by the International Conference on Harmonization (ICH) and in accordance with the ethical principles underlying European Union Directive 2001/20/EC. The study is conducted in compliance with the study-protocol. For the present study an EudraCT-Number (2018–001823-38) has been obtained. The final study protocol has been approved by the ethics committee of the Technical University of Munich, Germany (Protocol Number AB 65/18) as well as by the responsible German government authority Paul-Ehrlich-Institute, Langen, Germany.

Investigators will ensure that patients are clearly and fully informed about the purpose, potential risks, and other critical issues regarding clinical studies in which they volunteer to participate. The informed consent form will adhere to the ethical principles that have their origin in the Declaration of Helsinki. All collected data from patients with signed informed consent will be entered into the electronic Case Report Form by the investigator. Sponsor representatives will review data centrally to identify potential issues to determine a schedule of on-site visits for targeted review of study records. In addition, the study may be evaluated by sponsors internal auditors and government inspectors who must be allowed access to Case Report Form, source documents, other study files, and study facilities.

Data collection and management will be performed according to general data protection regulation of the European Union.

## Discussion

RACE IT study aims to evaluate immunotherapy with the PD-1 checkpoint-inhibitor Nivolumab combined with radiation therapy followed by radical cystectomy for patients with locally advanced bladder cancer.

Survival rates of patients with locally advanced bladder cancer treated with radical cystectomy are poor. The addition of neoadjuvant chemotherapy could increase 5-year survival only about 5–8% [2, 6] indicating the need for novel additional therapies. Retrospective analyses have shown promising results for the use of RCHT in the neoadjuvant setting, with 5-year disease specific survival (DSS) of 62% compared to 27% in their historical “cystectomy only” cohort [17]. Around 50% of patients are ineligible to receive neoadjuvant chemotherapy mainly because of impaired renal function [4], thus ongoing trials evaluate the benefit of immune-checkpoint inhibitors in a neoadjuvant setting since they can be given regardless of kidney function. An Open-Label, Single-Arm, Phase II Study (PURE-01) analyzed the activity of pembrolizumab as neoadjuvant immunotherapy before radical cystectomy for MIBC and showed downstaging to pT < 2 in 54% of patients and 42% pT0-patients in RC after 3 cycles of pembrolizumab. Notably, all 55 patients enrolled in the study underwent radical cystectomy [22]. Three patients (6%) had grade 3 AEs (diarrhea, hyperkaliemia, ALT/AST-increase) that caused pembrolizumab discontinuation for one patient. Response rates were significantly dependent on the PD-L1 status (highly enriched in patients with PD-L1 CPS ≥ 10% vs. no appreciable antitumor effects patients with CPS < 10%) and significant association between tumor mutation burden (TMB) and pT0 was observed. Interim results of the ABACUS-trial showed that neoadjuvant atezolizumab is safe and associated with a significantly improved pathological CR (29%). Treatment related grade 3/4 toxicity occurred in 12% of patients and 7 out of 69 patients (10%) did not have cystectomy [13].

These studies show promising results with high rates of downstaging, but the responses were significantly dependent on the PD-L1 status [22]. Response rates might even be increased with concomitant radiation therapy, which leads to immunogenic cell death, release of T-cell attracting cytokines and upregulation of surface molecules. There is preliminary evidence to believe that the combination of radiation therapy with immunomodulating drugs has a promising potential for synergistic and off-target effects, without severe toxicities and might improve downstaging and operability of the tumor [18, 19]. We believe that response and survival rates might be improved due to the promising results of immunomodulating agents in MIBC and metastatic bladder cancer as well as the possible synergistic effects of radiation therapy and PD-1 inhibition.

One critical point of neoadjuvant therapy in general is the delay or even truncation of definitive therapy. This study holds a risk of delay of surgery and consecutive progression-risk for patients. In the PURE-01 trial the neoadjuvant administration of immunotherapy did not delay planned surgery [22]. Available data and clinical experience suggest, that the combination of radiation and immunotherapy is well tolerated and does not lead to excess toxicity [18].

The experience with preoperative RCHT in the setting of trimodal therapy shows reasonable anti-tumor activity [17]. Therefore, we assume that our planned treatment will at least contribute to inhibition of tumor progression. And due to the poor prognosis of this patient population, we would accept the risk of a delay compared to immediate cystectomy or neoadjuvant chemotherapy, given the expected benefit.

In concern of organ specific toxicities, especially gastrointestinal toxicity is a potential risk for patients, which cannot be quantified due to the lack of high quality data in the setting of combined radioimmunotherapy.

Follow-up is limited to 1 year after cystectomy, but we have to emphasis that in this trial the DFS and OS are secondary objectives. Due to the fact, that most recurrence occur in the first year after surgery, the one-year DFS and OS rates as secondary endpoints will provide sufficient data of treatment efficacy in order to plan a consecutive phase III trial.

We will perform this trial to evaluate the combined approach of radiation therapy with a PD-1 checkpoint-inhibitor followed by radical cystectomy to analyze the feasibility of this therapy concept and to generate first efficacy data for a possible future phase III trial.

## Trial status

The trial has started recruitment in February 2019.

## Data Availability

Not applicable.

## Abbreviations

CR: Complete response
CSS: cancer specific survival
CTLA-4: Cytotoxic T-lymphocyte associated protein 4
DFS: Disease free survival
ECOG: Eastern Cooperative Oncology Group
FAS: Full Analysis Set
GCP: Good Clinical Practice
Gy: Gray
ICH: International Conference on Harmonization
MIBC: Muscle-invasive bladder cancer
OV: Overall survival
PD-1: Programmed cell death protein 1
PD-L1: Programmed death ligand-1
PEI: Paul-Ehrlich Institut
RC: Radical cystectomy
RCHT: radiochemotherapy
SOP: Standard Operating Procedure
TMT: Trimodal therapy
